**Methods:**

This will be a placebo run-in, randomized controlled trial. After the 1-week sham acupuncture intervention run-in period, the 80 eligible IBS patients without strong placebo responses will be randomly assigned to the true acupuncture (TA) group and sham acupuncture (SA) group. During the 4-week intervention period, all patients will receive the assigned intervention three times per week, followed by an 8-week follow-up. The primary endpoint is the response rate, defined as the proportion of patients with a decrease of greater than or equal to 50 points in the IBS Symptom Severity Scale (IBS-SSS) score from baseline at week 4. Secondary outcomes include the response rates at other time points, original IBS-SSS scores, Hospital Anxiety and Depression Scale (HADS), Visual Analog Scale (VAS) for abdominal pain, satisfaction with bowel habits, blinding assessment, and Credibility/Expectancy Questionnaire. Safety will be monitored and recorded during the trial.

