#### Secondary outcomes

2.7.2

Original IBS-SSS scores will be assessed as secondary outcomes at baseline and at weeks 2, 4, 8, and 12. The response rate will also be evaluated as a secondary outcome at baseline and at weeks 2, 8, and 12.

Hospital Anxiety and Depression Scale (HADS) (22). Symptoms of anxiety and depression will be assessed using the HADS at baseline and at week 2, 4, 8, and 12. The HADS is a validated 14-item instrument comprising two subscales for anxiety and depression. Scores are interpreted as follows: 0–7, no symptoms; 8–10, suspected symptoms; and 11–21, definite symptoms (23).

Visual Analog Scale (VAS) (24). The worst abdominal pain over the preceding 24 hours will be evaluated by VAS (0–10), with 0 indicating no pain and 10 indicating the worst imaginable pain. VAS will be evaluated at baseline and at week 2, 4, 8, and 12.

Satisfaction with bowel habits (25). Patients’ satisfaction with defecation will be assessed using a 7-point Likert scale, with response options ranging from “strongly disagree” to “strongly agree.” This scale provides an appropriate balance between sensitivity and usability, allowing for more nuanced assessment than a five-point scale while avoiding the cognitive burden of scales with more response options. Assessments will be conducted at baseline and at week 2, 4, 8, and 12.

Credibility/Expectancy Questionnaire (26). The credibility and expectancy to the intervention will be measured within 5 minutes after the first intervention session completed.

Blinding. The blinding assessment will be conducted by asking participants to guess their intervention allocation at week 2 and 4.

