#### Statistical analysis

2.11

The following hypothesis will be tested simultaneously for the primary outcome:

H0: There is no difference in the response rate between the TA and SA group.

H1: There is a significant difference in the response rate between the TA and SA group.

Analyses of the treatment efficacy will be based on the modified intention-to-treat (mITT) population, which consists of all participants who were randomized and had baseline data. The safety analysis will be carried out on the safety population, which comprises individuals who received at least one dose of treatment after randomization with full recorded safety outcome. The incidence of adverse events will be determined by dividing the number of patients who experienced at least one adverse event by the total number of patients. Missing data in outcomes will be imputed five times by multiple imputation method, with the mean values been used for analysis. Continuous data will be presented as mean and standard deviation or as median and interquartile range, while categorical data will be presented in frequency and proportion. For response rate, comparison will be performed using chi - square test. For other endpoints, continuous variables will be compared using T test or the Wilcoxon rank sum test, and categorical variables will be examined using the chi - square test or Fisher’s exact test. To assess the robustness of the findings, sensitivity analyses will be conducted by truncating the data at the first use of rescue medication in repeated-measures models, and by including rescue medication and demographic characteristics use as covariates to control for its potential impact on the treatment effect estimate. Subgroup analyses will be conduct on patients with different subtypes of IBS (IBS with diarrhea, IBS with constipation, IBS with mixed bowel habits, and IBS unclassified) to evaluate the differences in the efficacy of acupuncture. All analysis will be two side and conducted using SAS 9.3 software, and a *P* value less than 0.05 will be considered statistically significant.

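### The general outcome rules would impute missing allocation guesses and reduce the blinding check to a between-arm P value that does not show which arm is unblinded

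*Protocol article*

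**What the plan says.** Secondary outcomes (2.7.2) includes the allocation guess: "The blinding assessment will be conducted by asking participants to guess their intervention allocation at week 2 and 4". The abstract does the same, naming "satisfaction with bowel habits, blinding assessment, and Credibility/Expectancy Questionnaire" among the secondary outcomes.

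Statistical analysis (2.11) has no sentence specific to the guess. Its general sentences are:

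- Missing data: "Missing data in outcomes will be imputed five times by multiple imputation method, with the mean values been used for analysis".
- Endpoints other than the primary: "categorical variables will be examined using the chi - square test" or Fisher's exact test.
- Description: "categorical data will be presented in frequency and proportion".
- Significance: "All analysis will be two side and conducted using SAS 9.3 software, and a *P* value less than 0.05 will be considered statistically significant".

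None of these excepts the blinding assessment.

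**The concern.** A guess is a report of what the patient believed at a visit. A value modelled from patients who stayed is not such a report, and those who left may have left partly because of what they believed. The documents do not say whether that will happen, but the imputation rule would hide it if it did.

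The comparison rule asks only whether the two arms guess differently. A blinding check also has to say in which arm patients recognised their treatment, and how strongly.

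The design makes recognition in one arm plausible. Every patient first has a week of sham by the SA procedure (Run-in period, 2.4). SA patients then carry on unchanged. TA patients move to other points, with deep needling at the abdominal and leg points and repeated manipulation to obtain deqi (Interventions, 2.6). The acupuncturists know the allocation (Blinding, 2.5.1), and the primary outcome is a patient-rated symptom score (2.7.1). The guess is the only stated measure of allocation belief at week 4, when the primary endpoint is taken. A non-significant P value, partly built on imputed answers, could be misread as evidence that blinding held.

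**Working it through.** **Inputs.** Sample size (2.10) gives 25% v 60% response, 80% power, alpha 0.05, 36 per group and 80 in total after 10% dropout. Allocation is 1:1 (2.5). The documents give no guess rates and no response options for the guess. All guess rates below are assumptions, and a two-way answer with no 'don't know' option is assumed.

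**Step 1: the plan's own figure.** The uncorrected two-proportion formula is n = [1.96·√(2·0.425·0.575) + 0.8416·√(0.25·0.75 + 0.60·0.40)]² / 0.35² = (1.370 + 0.550)² / 0.1225 = 30.1, so 31. With the continuity correction, (30.1/4)·[1 + √(1 + 4/(30.1·0.35))]² = 35.6, so 36, which matches. Then 36/0.90 = 40 per arm, 80 in total. The blinding check will therefore rest on about 36 to 40 answers per arm. No power is stated for it.

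**Step 2: imputation.** The mean of five yes/no imputations is one of 0, 0.2, 0.4, 0.6, 0.8 or 1. Four of the six values are fractions, and these cannot be counted in a chi-square or Fisher table.

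**Step 3: does the P value identify the arm?** For a 2×2 table with 40 per arm, chi-square = N(ad − bc)² / (product of the four margins).

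- A: TA 30/40 and SA 20/40 guess 'true': 80·(30·20 − 10·20)² / (40·40·50·30) = 12,800,000 / 2,400,000 = 5.33, P = 0.021.
- B: TA 20/40 and SA 10/40 guess 'true': 80·(20·30 − 20·10)² / (40·40·30·50) = 5.33, P = 0.021.

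The Bang index is BI = 2p − 1, where p is the share guessing correctly in the arm, with SE = 2√(p(1 − p)/n).

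- A: TA 0.50 (0.23 to 0.77), SA 0.00 (−0.31 to 0.31).
- B: TA 0.00 (−0.31 to 0.31), SA 0.50 (0.23 to 0.77).

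The test statistic is the same, but the arm affected is the opposite one.

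**Step 4: sensitivity when one arm is unblinded.** Assume 70% of TA and 50% of SA patients guess 'true'.

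- Between-arm test, n = 40: Φ[(0.20 − 1.96·√(2·0.6·0.4/40)) / √((0.21 + 0.25)/40)] = Φ[(0.20 − 0.2147)/0.1072] = 44.5%. At n = 36: 40.8%.
- TA arm against 50%, n = 40: Φ[(0.20 − 1.96·0.5/√40) / √(0.21/40)] = Φ[(0.20 − 0.1550)/0.0725] = 73.3%. At n = 36: 68.4%.

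**Step 5: sensitivity when both arms are equally unblinded.** The ranges run from 36 to 40 per arm.

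| Guess 'true', TA/SA | Between-arm test | Test in one arm |
|---|---|---|
| 60/40 | 39-43% | 22-24% |
| 65/35 | 73-78% | 43-47% |
| 70/30 | 94-96% | 68-73% |

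Here the between-arm test is the more powerful of the two.

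**Step 6: precision of the arm-level index.** The half-width is 1.96·2·√(p(1 − p)/n). For p = 0.75 it is 0.27 (n = 40) or 0.28 (n = 36). For p = 0.50 it is 0.31 or 0.33.

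**The case against.** The strongest reply is that section 2.11 never mentions the guess. The plan described here comes from combining a list of secondary outcomes with two general sentences, in a condensed article whose analysis plan is not shown. The absence of a blinding index is indeed no finding. What stands is that the article states rules for all outcomes, makes no exception, and those rules do not suit this item. The documents do not show that the investigators intend to impute guesses. The phrase about mean values might also mean pooled estimates; the fractions would then disappear, but the modelled guesses would remain.

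Four stronger readings are tempting and are not supported:

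- A reader might infer that the check has low power in general. It does not: power is 73-78% at 65/35 and 94-96% at 70/30, and the between-arm test beats an arm-level test under symmetric unblinding. The main limit is 36 to 40 patients per arm, which no change of summary removes.
- A reader might infer that a single chi-square test is planned. The text allows chi-square or Fisher's exact test, and the guess is taken at two visits.
- A reader might infer that the unblinded arm could not be seen at all. Categorical data are to be shown as frequencies and proportions, and guess proportions by arm would separate examples A and B. Only the P value fails to do so.
- A reader might infer that the guess is the only check on expectancy. A Credibility/Expectancy Questionnaire is given after the first session (2.7.2).

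It is also fair to say that no passage sets a decision rule for the guesses or states that a non-significant result will be taken as intact blinding. That risk is one of interpretation.

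**Conclusion.** The point holds in a limited form. As written, the general rules cover the guess, would impute answers never given, and would test the arms with a P value that is identical for unblinding confined to TA and unblinding confined to SA (5.33, P = 0.021 in both examples). If one arm alone is unblinded at an assumed 70% v 50%, the between-arm test has 41-45% power against 68-73% for an arm-level test. That comparison assumes uninformed patients would guess evenly and that no 'don't know' answer is offered. Because some patients may guess 'true' whatever they receive, the two arm-level indices must be read together.

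This is a minor point. It changes no efficacy estimate, error rate or sample size, but it affects how well the trial can answer a doubt about blinding in a patient-rated primary outcome.

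**What to change.** Add to Statistical analysis (2.11):

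- Allocation guesses at weeks 2 and 4 are exempt from multiple imputation and are analysed as observed.
- The number of each answer and the number missing are shown by arm at each visit.
- The Bang blinding index with its 95% CI is reported separately for TA and SA, and blinding is judged from the size of both indices and their intervals.
- A between-arm P value above 0.05 is not taken as evidence that blinding held.

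If a 'don't know' answer is offered, say so and use the form of the index that allows for it.

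The cost is a few sentences, with no further data or visits. The downside is that the intervals will be wide, about ±0.27 to ±0.33 at 36 to 40 per arm, and will show openly that the check is imprecise.

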#### Rescue medicine

2.6.3

Participants will be instructed to maintain their usual diet and lifestyle throughout the study. When necessary, loperamide or polyethylene glycol 4000 will be permitted as rescue medication under the individualized guidance of a gastroenterologist. Furthermore, psychiatric specialists will be arranged to assess whether additional treatment is required based on patients’ scale scores and disease status, not limited to pharmacotherapy. Any use of rescue medication or other concomitant treatments will be documented, including measure, time and dosage.

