#### Primary outcome

2.7.1

The primary outcome will be the response rate, defined as the proportion of patients achieving a reduction of ≥50 points in the IBS-SSS (20) from baseline, which is recommended by the U.S. Food and Drug Administration (21). The primary endpoint will be the between-group comparison of response rate at week 4. The IBS-SSS consists of five items rated on a visual analog scale (0–100): severity of abdominal pain, frequency of abdominal pain, severity of abdominal distension, dissatisfaction with bowel habits, and interference with quality of life. Each item contributes equally to the total score, with an overall range of 0–500.

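### Rescue medication used after randomisation should not be a covariate in the sensitivity analysis of the treatment effect

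*Protocol article*

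**What the plan says.** Section 2.7.1 fixes the primary endpoint: "The primary endpoint will be the between-group comparison of response rate at week 4", with response meaning a fall of at least 50 points in IBS-SSS. Section 2.11 gives the test: "For response rate, comparison will be performed using chi - square test". The efficacy population is the modified intention-to-treat set, "which consists of all participants who were randomized and had baseline data". As written, this primary comparison is unadjusted and uses week-4 response whether or not rescue was taken, although the article does not say so in words.

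Section 2.11 then adds two sensitivity analyses, introduced by "To assess the robustness of the findings":

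- **Truncation:** "truncating the data at the first use of rescue medication in repeated-measures models".
- **Covariate adjustment:** "by including rescue medication and demographic characteristics use as covariates to control for its potential impact on the treatment effect estimate".

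Section 2.6.3 permits loperamide or polyethylene glycol 4000 on need, guided by a gastroenterologist. It also provides that "psychiatric specialists will be arranged to assess whether additional treatment is required". Rescue and other concomitant treatments are all recorded, with their timing and dose.

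**The concern.** A covariate in a randomised comparison should be fixed before randomisation. Rescue use during treatment is not: a patient takes it because symptoms persist, and symptoms are what acupuncture is meant to change. It can therefore lie on the path from treatment to outcome. It also shares causes with the outcome, because a more severely affected patient is both more likely to need rescue and less likely to respond.

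Once rescue is in the model, TA users are compared with SA users, and TA non-users with SA non-users. These are not like-for-like groups. If TA reduces the need for rescue, the TA patients who still take it are on average a more severe selection than the SA patients who take it. The adjusted coefficient is then not the total effect of treatment and, without further assumptions, not a direct effect either.

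At stake is how the trial's robustness statement is read. A sound primary result could look fragile because the adjusted estimate is smaller. A match between the two estimates would not be reassuring either, because they answer different questions.

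**Working it through.** **The plan's own figure.** Section 2.10 gives 25% (SA) against 60% (TA), two-sided α = 0.05 and 80% power, with 36 per group.

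- Uncorrected: n = [1.960·√(2·0.425·0.575) + 0.842·√(0.25·0.75 + 0.60·0.40)]² / 0.35² = 30.1, rounded up to 31.
- With continuity correction: (30.1/4)·[1 + √(1 + 4/(30.1·0.35))]² = 35.6, rounded up to 36.
- Dropout: 36/0.90 = 40 per group, 80 in total.

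The stated figure reproduces, and nothing below changes it.

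**Illustration of the bias.** The documents give no rescue rates, so everything here beyond the 25% SA response rate is assumed. T is the arm (1 = TA). U, e₁ and e₂ are independent standard normal, and U is unmeasured severity.

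- Rescue: R = 1 if U − d·T + e₁ > 0.9.
- Improvement: d·T − U + b·R + e₂, where b is the benefit of rescue itself.
- Response: Y = 1 if improvement exceeds the SA 75th percentile, so SA response is 25%.

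The assumed rescue rates follow directly. SA is 1 − Φ(0.9/√2) = 1 − Φ(0.636) = 0.26. TA at d = 1.3 is 1 − Φ(2.2/√2) = 1 − Φ(1.556) = 0.06.

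Y was regressed on T alone and on T plus R, with 400,000 simulated patients per row. SA rescue is 26% throughout.

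| d | b | TA rescue | TA response | Risk difference, T only | Risk difference, T and R | Change |
|---|---|---|---|---|---|---|
| 1.3 | 0 | 6% | 59.6% | 0.346 | 0.290 | −16% |
| 1.3 | 0.5 | 6% | 58.2% | 0.332 | 0.294 | −11% |
| 1.3 | 1.0 | 6% | 55.9% | 0.309 | 0.295 | −5% |
| 1.0 | 0 | 9% | 51.2% | 0.262 | 0.214 | −18% |
| 1.0 | 1.0 | 9% | 48.1% | 0.231 | 0.219 | −5% |
| 0.5 | 0 | 16% | 37.3% | 0.123 | 0.096 | −22% |
| 0.5 | 1.0 | 16% | 35.7% | 0.107 | 0.100 | −7% |

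The first row is close to the planning values. There the change is (0.290 − 0.346)/0.346 = −16%, and the odds ratio falls from 4.42 to 3.58. Since b = 0 in that row, rescue does nothing to the outcome, so the whole shift is an artefact of conditioning on it.

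**Null case.** Here treatment lowers rescue use but has no effect on response, and rescue has no effect either (1,000,000 patients per row).

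| SA rescue | TA rescue | Risk difference, T only | Risk difference, T and R |
|---|---|---|---|
| 26% | 26% | 0.001 | 0.001 |
| 26% | 16% | 0.001 | −0.023 |
| 26% | 9% | 0.001 | −0.040 |
| 26% | 4.5% | 0.001 | −0.050 |

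Adjustment creates a difference against TA where none exists. The bias disappears when rescue use is equal in the two arms, which confirms the mechanism.

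**The case against.** Several points on the other side stand.

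- **The primary is untouched.** It is an unadjusted chi-square test in randomised patients. A covariate in a supporting analysis cannot alter its estimate, its error rate or the sample size.
- **Only one of the two analyses adjusts for rescue.** A reader might infer that neither can speak to robustness. The text does not support that. Truncation at first rescue discards later values, so a week-4 response reached after loperamide or polyethylene glycol is not used. It addresses a no-rescue question under a missing-at-random assumption.
- **A different model is not a fault.** The article speaks of the findings generally, and several outcomes are measured repeatedly. A repeated-measures model for binary response with a week-4 contrast would also fit the wording, and its form may be settled in an analysis plan that is not shown.
- **Psychiatric treatment may be covered.** A reader might infer that it is ignored. It sits under the rescue heading in section 2.6.3 and is recorded, but that section words it separately from rescue medication. Whether section 2.11 includes it is ambiguous, not shown to be omitted.
- **The demographic covariates are acceptable.** They are fixed before randomisation.
- **The figures are illustrative.** The rescue rates are assumed, and the shrinkage narrows as rescue becomes more effective (16%, 11%, then 5% at d = 1.3), so neither its size nor its direction is guaranteed.

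One defence does not stand. Rescue taken before randomisation would be a legitimate covariate, but the article does not restrict the covariate to that, and its stated aim of controlling an impact on the treatment effect points to use during treatment.

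**Conclusion.** The point holds for the covariate analysis alone. Entering rescue use in the treatment-effect model conditions on something treatment can change, and the result cannot serve as a check on the primary.

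Under the assumptions shown (SA rescue about 26%, TA 4–16%, shared unmeasured severity), a true risk difference of about 0.35 is reported as about 0.29, and a null effect as −0.02 to −0.05. With 40 per arm, the standard error of the risk difference at the planning rates is √[(0.25·0.75 + 0.60·0.40)/40] = 0.103. The shift of 0.056 is thus about half a standard error: not enough to overturn a large effect, but systematic and liable to be misread. If the arms do not differ in rescue use, there is no bias under the null.

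It would go too far to conclude that the primary result is compromised or that the plan has no usable check on rescue. This is a correction to one stated supporting analysis, worth making before the data are seen.

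**What to change.** In section 2.11, or in the analysis plan that implements it:

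1. Remove rescue use from the covariates. Keep only pre-randomisation ones, such as demographics and baseline IBS-SSS.
2. State that the primary analysis counts week-4 response regardless of rescue.
3. Replace the covariate analysis with one on the same binary endpoint and the same test, in which response also requires no recorded rescue medication between randomisation and week 4. Run a further variant that also requires no newly started psychiatric treatment, which would settle the ambiguity over that treatment.
4. Keep the truncation analysis, labelled as a no-rescue analysis under missing at random.
5. Report rescue use by arm.

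The cost is small. Section 2.6.3 already has the needed data recorded, and neither the sample size nor the clinical handling of rescue changes. If the change is judged important, section 4 requires ethics committee approval. One downside should be stated: the composite targets a different quantity from the primary, and its psychiatric variant depends on individual specialist decisions, so both must be labelled as supportive.

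### One of the two rescue-medication robustness analyses adjusts for rescue use, which treatment can change after randomisation, so it cannot show whether the week-4 result is robust

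*Protocol article*

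**What the plan says.** The Primary outcome section fixes one binary comparison at one visit: "The primary endpoint will be the between-group comparison of response rate at week 4". A responder is a patient whose IBS-SSS falls by at least 50 points from baseline. The Statistical analysis section tests it without adjustment: "For response rate, comparison will be performed using chi - square test".

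The Rescue medicine section states that "loperamide or polyethylene glycol 4000 will be permitted as rescue medication" when needed, with a gastroenterologist's guidance, and that the time and dose of any such use are recorded.

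The Statistical analysis section then says: "To assess the robustness of the findings, sensitivity analyses will be conducted". Two are named. The first works by "truncating the data at the first use of rescue medication in repeated-measures models". The second works "by including rescue medication and demographic characteristics use as covariates to control for its potential impact on the treatment effect estimate". The protocol gives no expected rescue rate for either arm.

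**The concern.** A covariate can safely be adjusted for in a randomised comparison if treatment cannot have altered it. Rescue use does not meet that condition. It occurs after allocation and follows symptoms, and symptoms are what the trial hopes to change. Entering it next to the arm term does two things:

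- It compares users with users and non-users with non-users. If treatment lowers rescue use, those who still need rescue on true acupuncture (TA) are a more severe group than those who need it on sham acupuncture (SA). Within each stratum, randomisation no longer balances severity.
- If acupuncture works and so reduces rescue use, part of the arms' real difference is credited to the rescue term.

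The adjusted estimate therefore differs from the randomised contrast even when rescue has no effect on the outcome. At stake is how the trial is read. A sound primary result could be reported as not robust, and agreement between the two analyses would be taken as reassurance that it does not give.

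**Working it through.** **Inputs from the protocol (Sample size section).** Response 25% on SA and 60% on TA; α = 0.05; 80% power; 36 per group; 10% dropout; 80 in total. The Statistical analysis section makes tests two-sided.

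**The plan's own figure.** Let p̄ = (0.25 + 0.60)/2 = 0.425 and Δ = 0.35.

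- Uncorrected n = [1.96·√(2·0.425·0.575) + 0.8416·√(0.25·0.75 + 0.60·0.40)]² / 0.35² = (1.370 + 0.550)² / 0.1225 ≈ 30.1, so 31.
- With continuity correction: (30.1/4)·[1 + √(1 + 4/(30.1·0.35))]² ≈ 35.6, so 36 per group.
- 36/0.90 = 40 per group, 80 in total.

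The stated size reproduces. The present point does not change it.

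**Assumed model.** The protocol gives no rescue rates, so these are assumptions. A latent severity U ~ N(0,1) is shared by both processes:

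- logit P(rescue) = a(arm) + g·U
- logit P(response) = b(arm) − h·U

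Here g and h are each 1 or 2 per SD, and a and b are set to give the chosen rescue rates and the protocol's 60% and 25%. Rescue does not enter the response equation, so it is inert and the true difference is 35 points. The adjusted estimate comes from a logistic regression of response on arm and rescue, standardised to the pooled rescue rate.

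**One case that can be checked by hand.** Rescue is 15% TA and 40% SA, pooled 27.5%. The model gives these response rates within strata:

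| g = h | Rescue users, TA v SA | Non-users, TA v SA | Weighted difference |
|---|---|---|---|
| 1 | 44.5% v 17.2% | 62.7% v 30.2% | 0.275·27.2 + 0.725·32.6 ≈ 31.1 |
| 2 | 23.7% v 8.3% | 66.4% v 36.2% | 0.275·15.4 + 0.725·30.2 ≈ 26.2 |

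For g = h = 1 the crude rates are 0.15·44.5 + 0.85·62.7 ≈ 60% and 0.40·17.2 + 0.60·30.2 ≈ 25%. The 35-point difference is intact before adjustment and reduced after it, although rescue does nothing.

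**Range over assumed rescue rates.** The last column is the share of simulated trials, at 36 per arm, in which the unadjusted test is significant and the rescue-adjusted test is not.

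| Rescue TA v SA | Adjusted difference (true 35) | Primary significant, adjusted not |
|---|---|---|
| 40% v 40% | 35 | 1–2% |
| 15% v 20% | 33–34 | 2–4% |
| 10% v 20% | 32–33 | 4–6% |
| 15% v 40% | 26–31 | about 10–24% |
| 10% v 50% | 20–29 | about 23–47% |

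A separate model, linear in probability with 40% rescue on SA, moves in the same direction by less: 35.5 points falls to about 31 at 15% TA rescue and about 30 at 11%. If TA used more rescue than SA, the shift would go the other way.

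**The case against.** **Size.** The documents give no rescue rates, and the larger distortions need a wide gap between arms. At 15% v 20% the loss is 1–2 points, and with equal use there is none. This stands, so the size can only be given as a range. The fault in the method does not depend on it, because the stated purpose is to control the effect estimate and this adjustment does not do that.

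**No true effect.** A reader might infer that the covariate would create an effect where none exists. The same model gives a spurious 3–6 points against TA at 15% v 40% rescue with 25% response in both arms. But if treatment changes no symptoms and patients are blinded, rescue use should be similar in both arms and the bias close to zero. I do not rely on that case.

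**Truncation.** A reader might also infer that the truncation check cannot test the primary result, since no main analysis uses a repeated-measures model. The documents do not support that:

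- The model's outcome is not named. Response is assessed at weeks 2, 4, 8 and 12, so a model of the binary response could give a week-4 contrast.
- Rescue first used during follow-up leaves the week-4 value in place.
- Comparing only unrescued patients at week 4 can look badly biased: with 25% response in both arms, all rescue users non-responders and rescue 30% v 10%, 0.25/0.70 − 0.25/0.90 ≈ 8 points. That is a complete-case calculation. A likelihood-based repeated-measures model also uses values before rescue.
- Truncation is itself an analysis that does not credit a response reached after rescue, so it would be wrong to say that such responses are never questioned.

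**A later analysis plan.** It could supply model details, but it could not make the covariate sound without departing from what the protocol states.

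**Conclusion.** The covariate analysis is wrong as written. It conditions on a variable that treatment can change, so neither agreement nor disagreement with the week-4 chi-square result is evidence on robustness. Under the assumptions above (shared severity, inert rescue, less rescue use on TA), a true 35-point difference shrinks by 1 to 15 points, according to how far rescue use differs between arms, and by nothing if it does not differ.

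The primary test, its P value and the sample size are untouched. Adjustment for demographic characteristics measured at baseline is sound. The truncation analysis is underspecified in this article but legitimate as a supplementary analysis. The change should be made before database lock, but the point does not threaten the main result.

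**What to change.** - Delete rescue use from the covariates and keep only covariates measured before randomisation.
- Add a repeat of the week-4 responder comparison in which patients who used rescue medication in a window before the week-4 IBS-SSS count as non-responders. Fix the window before database lock.
- Report rescue use by arm as a result in its own right.
- The truncation analysis may stay. Label it supplementary, say that it estimates the outcome had rescue not been used, and have it report the week-4 response contrast so that it can be set beside the primary result. Replacing it outright would be a choice between recognised strategies, not a correction.

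The cost is wording in the analysis section. Time and dose of rescue use are already to be recorded, and no rule on rescue treatment changes. The downside is that the non-responder analysis lowers the response rates in both arms and answers a slightly different question: response without recent rescue.
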